# Effects of improved sanitation on diarrheal reduction for children under five in Idiofa, DR Congo: a cluster randomized trial

**DOI:** 10.1186/s40249-017-0351-x

**Published:** 2017-09-19

**Keywords:** Sanitation, Diarrhea, Well-equipped latrine, Sanitation calendar

## Abstract

**Background:**

The lack of safe water and sanitation contributes to the rampancy of diarrhea in many developing countries.

**Methods:**

This study describes the design of a cluster-randomized trial in Idiofa, the Democratic Republic of the Congo, seeking evidence of the impact of improved sanitation on diarrhea for children under four. Of the 276 quartiers, 18 quartiers were randomly allocated to the intervention or control arm. Seven hundred and-twenty households were sampled and the youngest under-four child in each household was registered for this study. The primary endpoint of the study is diarrheal incidence, prevalence and duration in children under five.

**Discussion:**

Material subsidies will be provided only to the households who complete pit digging plus superstructure and roof construction, regardless of their income level. This study employs a Sanitation Calendar so that the mother of each household can record the diarrheal episodes of her under-four child on a daily basis. The diary enables examination of the effect of the sanitation intervention on diarrhea duration and also resolves the limitation of the small number of clusters in the trial.

In addition, the project will be monitored through the ‘Sanitation Map’, on which all households in the study area, including both the control and intervention arms, are registered. To avoid information bias or courtesy bias, photos will be taken of the latrine during the household visit, and a supervisor will determine well-equipped latrine uptake based on the photos. This reduces the possibility of recall bias and under- or over-estimation of diarrhea, which was the main limitation of previous studies.

**Trial registration:**

The study was approved by the Institutional Review Board of the School of Public Health, Kinshasa University (ESP/CE/040/15; April 13, 2015) and registered as an International Standard Randomized Controlled Trial (ISRCTN: 10,419,317) on March 13, 2015.

**Electronic supplementary material:**

The online version of this article (doi:10.1186/s40249-017-0351-x) contains supplementary material, which is available to authorized users.

## Multilingual abstracts

Please see Additional file 1 for translations of the abstract into the five official working languages of the United Nations.

## Background

As of 2010, 1.731 billion episodes of diarrhea in children aged under five were reported globally [1]. Diarrhea killed 0.578 million children, accounting for 9.2% of all child deaths in 2013 [2]. In developing countries, the high prevalence of diarrhea can be attributed to the lack of safe water and sanitation [3]. The world has made huge strides in achieving the MDG target for safe water coverage over the past decade, meeting the target ahead of schedule in 2010. However, sanitation remains an important challenge for the global development agenda, with the coverage still below the target of 77% [4, 5]. An estimated 2.4 billion people still do not have access to improved sanitation facilities in 2015, and of these, around 1 billion people still practice open defecation [6]. In addition, a huge disparity in sanitation coverage exists among regions and between urban and rural areas. In particular, people without access to improved sanitation facilities are concentrated in Southern Asia and sub-Saharan Africa [1]. The situation seems especially dire in sub-Saharan African countries; Southern Asia has increased coverage from 22% in 1990 to 49% in 2015, while sub-Saharan Africa’s coverage has risen from 24% to only 31% over the same period [4–6]. An urban–rural divide in access to sanitation also exists. Today, only 51% of the rural population has access to improved sanitation facilities worldwide, compared with 82% of the urban population [4–6].

In the Democratic Republic of the Congo (DRC), the mortality of children remains stubbornly high. As of 2013, out of 1000 births, 119 children aged under 5 years lost their lives. In particular, diarrheal diseases are the common causes of mortality, being responsible for approximately 11% of child deaths. Of all sub-Saharan African countries, only seven countries have a higher percentage of diarrhea-specific child death than that of the DRC [7]. The country also has lower water and sanitation coverage than other countries in sub-Saharan Africa. In 2012, the DRC was reported to be one of only three countries where less than half of the population had access to safe water sources [5]. Only 16% of total households in the country have access to improved sanitation, with 4% having access in rural areas in comparison with 36% in urban areas. This is even worse than the sub-Saharan African average of 44 and 24% in urban and rural areas, respectively [8].

The majority of previous studies exploring the effect of improved sanitation, however, were observational [9–12]. Furthermore, only a few studies have investigated the net effect of improved sanitation on diarrheal reduction for children aged under five. Cochran Review results [13] showed that previous studies have neither executed a cluster randomized control trial (cRCT) on sanitation intervention nor assessed the effects on intermediate outcomes, such as the presence of flies. The first study that employed a randomized trial to measure the health impact of large-scale sanitation programs [14] could not find any evidence on the protective effects of improved latrines against child diarrhea prevalence. In a similar vein, a recent cRCT study that employed process evaluation [15] could not find any evidence that increased sanitation coverage is effective in preventing diarrhea. However, it is important to note, as the authors did, that in a situation where the coverage of improved sanitation is not adequate, improved sanitation’s protective effects against diarrhea may not be properly observed. The sufficient level of latrine coverage is a necessary condition to determine the effect of improved latrines on diarrhea prevention, given diarrhea’s transmission characteristics and the phenomenon of herd protection [16]. Other recent trials [17–21] also revealed similar limitations with regard to low coverage of improved latrine uptake and use. However, according to Fuller and his colleagues [22–24], a sanitation intervention has the potential to provide herd protection against diarrheal diseases, effectively reducing the prevalence. Their mathematical modeling demonstrated that when their neighbors use improved sanitation, susceptible persons in a household would face a reduced probability of contracting a diarrheal infection regardless of their own sanitation practices [22]. Therefore, more trials should be conducted in contexts where the coverage level is sufficiently high to better measure and quantify the effects of improved latrines.

We aim to investigate the extent to which well-equipped latrines reduce child diarrhea, especially in the conditions where the latrine coverage reached an almost universal level, or the level required to generate herd protection. Improved latrines can prevent transmission of pathogens via flies, contaminated fields and water [25]. If latrines are not properly equipped, used and managed, they can be sources of potential disease transmission [26]. Therefore, reflecting the 5-f diagram, we will focus on which components latrines should have (pit-hole depth, pit-hole cover, cement slab, and hand-washing facility) and how they should be managed (feces around the pit-hole and flies) in order to disrupt disease transmission. As a secondary research question, we will explore the association of children’s diarrheal prevalence with latrine components (pit-hole depth, pit-hole cover, cement slab, and hand-washing facility) and latrine management (feces around the pit-hole and flies).

## Methods/design

### Study setting

The study site is located in the Idiofa Territory of the Kwilu District, Bandundu Province, 655 km away from Kinshasa, the capital city of the DRC (Fig. 1). The territory has five cities and 12 sectors with a population of 1.4 million. Despite the existence of diverse ethnic groups, the Mubunda tribe mainly dominates the territory, with many speaking the Kikongo language. Agriculture is the main source of income in the region.

**Fig. 1 Fig1:**
[figure not shown]
**a** The study area, **b** The study area

This water, sanitation and hygiene (WASH) project has been designed to reduce diarrhea among children under four by providing clean water, improving household latrines and promoting relevant hygiene practices. Since the construction and use of latrines by household members cannot be fully achieved without necessary behavioral changes, hygiene promotion was included as one of the activities under the project.

### Study design

This cluster-randomized trial takes a *quartier*, a subdivision of a village, as the randomization unit since well-equipped latrines have an impact on diarrhea transmission across households at a cluster level. A “well-equipped latrine” is defined as having (1) a pit with a depth of more than 1.5 m; (2) a superstructure; (3) a roof; (4) a cement slab; (5) a pit-hole cover; and (6) a hand-washing facility based on the UNICEF Healthy Village Programme in the DRC. Any latrine that does not meet a single requirement will not be defined as a well-equipped latrine in the trial. A *quartier* is the lowest administrative unit in the DRC, where the number of households ranges from 396 to 2873. All the interventions will be undertaken on a *quartier*-wide basis. Since the purpose of the intervention is to reduce diarrhea, a *quartier* will be an appropriate dimension for the transmission zone, where humans, vectors, and intermediate hosts are interacting with each other and sharing a common pool of parasites.

We will employ a phase-in design. For well-equipped latrines, the project will roll out only in an intervention arm for the first phase (8 months). A total of four rounds of household surveys (including the baseline survey) will be conducted every 6 months (June 2015, January and August 2016, and February 2017) throughout the trial. The second round of the survey will be conducted immediately before the control arm will receive the intervention for the next 6 months. After the intervention period, we will have a follow-up period of about 1 year in which the third and the fourth survey will be conducted.

A preliminary survey was conducted from March through May of 2013 to gather information and analyze conditions at the field level to develop the WASH project in the DRC. On the basis of the preliminary results, each *quartie*r was rated by the degree/intensity/severity of the needs in terms of quantity of safe water per person per day *(liter/person/day),* distance to water points from the *quartier* (*km*), and the percentage of households with a household latrine (%).

A two stage cluster sampling method was employed for this study. The 38 target *quartiers* in 12 villages for the project were selected based on the priority scored by degree of need, from which 18 *quartiers* in 10 villages were randomly chosen employing probability proportional to size (PPS). Eighteen *quartiers* were randomly allocated to the intervention or control arm according to the results of the baseline survey, which was conducted in January 2015.

The *quartiers* were allocated into blocks by administrative unit or village according to ‘restricted randomization’.Our study used restricted randomization since it involved selecting randomly from a smaller set of allocations fulfilling certain restrictions. We stratified the *quartiers* into three groups depending on the prevalence of child diarrhea, and within each stratum we grouped the *quartiers* into two for the following reasons: one is to ensure that *quartiers* in the same village be allocated to same arm; the other is to have the same number of *quartiers* for the intervention and control arm.

A *quartier* was selected as representative for each group in each stratum, and the leaders from the *quartier* participated in the randomization activity to select an envelope containing a paper marked O or X without knowing it. For instance, in Fig. 2, if the leader of *quartier* 1 selected an envelope with O, all the *quartiers* from Q1 through Q5 were to be allocated to the treatment group, and the others from Q6 through Q10 to the control group. Using this method, we could expect 8 different allocation scenarios for the trial.

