**Fig. 2 Fig2:**
[figure not shown]
Restricted randomization of the trial. This figure shows how we carried out restricted randomization for the study. We stratified *quartiers* depending on the child diarrheal prevalence, and within each stratum we grouped the *quartiers* into two (shown graded and ungraded in the figure) in order to ensure that *quartiers* in the same villages are allocated to the same arm and also to allocate the same number of *quartiers* to the treatment and control arms. *Quartiers* in the green boxes were selected as representative for each group in each stratum, and the leaders from the *quartiers* participated in the randomization activity, selecting an envelope containing a paper marked O or X without knowing which it would be before they opened it. For instance, if the leader of *Quartier* 1 selected an envelope with O, all the *quartiers* from Q1 through Q5 were to be allocated to the treatment group and Q6 through Q10 were remaining for the control group. Using this method, there were 8 different possible allocation scenarios for the trial. (Village and quartier name) V1: Bangabanga, V2: Bwalenge, V3: KalangandaMukeni, V4: Mayanda, V5: Ingundu, V6: ImpiniNnsi, V7: Punkulu, V8: IntswemLabwi, Q1: Bangabanga1, Q2: Bangabanga2, Q3: MbuluEbeth, Q4: Mbulesal, Q5: Ibansi, Q6: Center, Q7: Lakam, Q8: Ndjili, Q9: Nganda, Q10: Orondi, Q 11: Camp Center de Sante, Q12: Camp Musanga, Q13: Ekong, Q14: ImbilEngwow, Q15: Tshikapa, Q16: BwalaNgundu, Q17: Eban, Q18: Sante Labwi2

One of the greatest limitations of restricted randomization lies in the risk that it could bring about biased estimates of effect, especially when there is any difference across the clusters in the possibility of allocation to any given treatment [27]. However, we believe the possibility of a biased result was quite low in our study because there was no difference across *quartiers* in their probability of allocation to the treatment or control arm (Fig. 3).

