Assuming a coefficient of variation of 0.3 with 80% study power and 7.5% diarrheal prevalence in the intervention resulted in seven clusters (7 *quartiers*) per each arm. We increased the number of clusters to nine each in the control and intervention arm, and sampled 360 households in each trial arm. We will follow up at least 12 weeks to make 8640 child-weeks (‘child-weeks’ is the unit of the denominator) in each *quartier* as required to meet 80% power, considering a 12.5% loss to follow-up.

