### Data analysis

Intention-to-treat analysis will be conducted to explore how well-equipped latrines reduce diarrhea incidence. To this end, the incidence density of diarrhea in children under four (diarrheal incidence per child-week, per child-month) and the reported diarrheal prevalence of the 7-day period will be calculated. Also, for other age groups (6–19, 20–39, 40 years and above), the reported diarrheal prevalence of the 7-day period will also be calculated. Generalized estimating equations will be used for the investigation at the cluster level. A log-binomial model will be used for calculating the incidence rate of diarrhea. The Random Effects model will be used, taking account of between-cluster variation based upon the assumption that there are cluster-level effects. Per-protocol analysis also will be conducted only as a contingency measure in cases where the coverage of latrines remains at an unexpectedly low level by the time when the intervention is completed. However, if we employ a per-protocol analysis, we cannot quantify the effects of well-equipped latrines, as this would break the comparability between the control and intervention groups obtained from randomization. Instead, we would note that per-protocol analysis is only an auxiliary analysis method to give additional background information. In addition, multi-level analysis will be conducted to investigate whether children living in the households without latrines could benefit from herd protection when a *quartier* reaches a certain level of latrine coverage (for instance, 70%).

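### Three draws allocated six village-based groups of quartiers, yet the power statement, and apparently the planned analysis, count 18 quartiers as independent allocated units

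*Protocol article*

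**What the plan says.** Methods/design, Study design, describes the quartier as "a subdivision of a village, as the randomization unit", and says that the eighteen quartiers "were randomly allocated to the intervention or control arm according to the results of the baseline survey".

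The same section then sets out the mechanism. Quartiers were put into three strata by child diarrhoea prevalence. Each stratum was split into two groups, partly to ensure that quartiers "in the same village be allocated to same arm" and partly to give equal numbers per arm. A leader from one representative quartier drew an envelope. In the worked example, one draw sends Q1 to Q5 to one arm and Q6 to Q10 to the other. The section states the consequence: "Using this method, we could expect 8 different allocation scenarios for the trial". The Fig. 2 legend repeats it: "there were 8 different possible allocation scenarios for the trial". The text after that legend discusses one risk of restricted randomisation, bias from unequal allocation probabilities, and sets it aside because every quartier had the same probability.

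The Sample size calculation works in independent quartiers, equates seven clusters with seven quartiers per arm, and ends: "We increased the number of clusters to nine each in the control and intervention arm". Under Data analysis: "Generalized estimating equations will be used for the investigation at the cluster level", together with a random-effects model for variation between clusters.

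**The concern.** Equal allocation probability for each quartier protects the estimate from bias. It does not make quartiers independent. Two quartiers in the same allocated group always share an arm, so whatever their villages have in common (water source, a local outbreak, local practice) moves with the arm as a block. An analysis that treats each quartier as a separate draw counts that common variation as independent noise.

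At stake are the standard error, p-value and power of the primary comparison. The Abstract and Discussion say that the daily calendar resolves the small number of clusters. More child-days reduce only the within-quartier sampling error and add no allocated units.

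Shared variation is plausible because groups are built from whole villages. Table 1 also shows arm differences in features that probably vary by place: time to fetch water (115 v 94 minutes), water quantity (50 v 65 litres) and unprotected source (98.6% v 94.6%). These do not measure the correlation in diarrhoea rates, and their printed p-values appear to be at household level.

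**Working it through.** **1. The plan's own figure.** Three strata with two opposed groups each, and one draw per stratum: 2 × 2 × 2 = 8 allocations. This reproduces the article. Allocated groups: 3 × 2 = 6, three per arm. Free 9:9 allocation of 18 quartiers would give C(18,9) = 48,620. The smallest p-value from a test over the actual allocations is 2/8 = 0.25 two-sided (1/8 = 0.125 one-sided).

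**2. Degrees of freedom.** Quartiers: 18 − 2 = 16, critical t 2.12. Six groups, unstratified: 6 − 2 = 4, critical t 2.78. Six groups with three strata: 6 − 3 − 1 = 2, critical t 4.30.

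**3. Inputs for the size of the effect.**
- Rates 0.100 and 0.075 per child-week (Sample size calculation).
- k = 0.20, an assumption taken from the article's own variance: √0.000401 / 0.1 = 0.200. The article prints 0.063 because it divides by 0.1 inside the root. It also mentions 0.3.
- y = 480 child-weeks per quartier: 720 households × 12 weeks / 18 quartiers.
- Group sizes: 5 v 5 is given for one stratum. The other eight quartiers are assumed to split 2 v 2 and 2 v 2.
- ρ, the share of between-quartier variance that is common within a unit: not in the article, so varied.
- Level of sharing: six groups cannot all be single villages, since the text gives 10 villages and the Fig. 2 legend names 8. Three cases were run: the whole group (5, 2, 2 per arm); 8 villages (each group of five split 3 + 2); 10 villages (split 2 + 2 + 1). The village splits are assumed.

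**4. Variance inflation.** The between-quartier part of an arm mean's variance is multiplied by F = 1 + ρ(Σn²/9 − 1), where n are the sizes of the sharing units in one arm.
- Whole group: Σn² = 25 + 4 + 4 = 33; F = 1.67 at ρ = 0.25, 2.33 at ρ = 0.5.
- 8 villages: Σn² = 9 + 4 + 4 + 4 = 21; F = 1.33, 1.67.
- 10 villages: Σn² = 4 + 4 + 1 + 4 + 4 = 17; F = 1.22, 1.44.

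**5. Type I error of a nominal 5% quartier-level t-test** (simulation with no effect, rate 0.1, k = 0.20, y = 480, 40,000 runs per cell):

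| Sharing within | ρ = 0 | ρ = 0.25 | ρ = 0.5 |
|---|---|---|---|
| Allocated group | 5% | 10% | 17% |
| 8 villages | 5% | 8% | 11% |
| 10 villages | 5% | 7% | 9% |

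At k = 0.30 the group-level row becomes about 5%, 12% and 19%. Group sizes of 5, 3, 1 give results close to 5, 2, 2.

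**6. Power for 0.100 v 0.075.** Variance of the difference: V = [(0.100 + 0.075)/480 + k²(0.100² + 0.075²)F]/9. At k = 0.20:
- F = 1: V = (0.000365 + 0.000625)/9, SE = 0.01049.
- F = 1.67 (group-level sharing, ρ = 0.25): V = (0.000365 + 0.001042)/9, SE = 0.01250, larger by a factor of 1.19. At ρ = 0.5 the factor is 1.36.

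Power by the noncentral t distribution:

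| k | Nine independent quartiers per arm, 16 df | Group-level ρ = 0.25, 4 df | Group-level ρ = 0.25, 2 df |
|---|---|---|---|
| 0.063 | 93% | 74% | 47% |
| 0.20 | 61% | 34% | 22% |
| 0.30 | 39% | 20% | 14% |

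The last two columns are approximate: group sizes are unequal, and any precision gained by removing stratum variance is not credited.

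**The case against.** The strongest case against the point is that the size of the problem depends on a correlation that the article never gives. With none, the quartier-level t-test runs at about 5% and is sound as a model-based test. That stands, so the point is conditional. It also matters where the sharing sits: within 8 or 10 villages the excess error is roughly half, or less, of what it is when the whole group shares.

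A reader might infer more than the document supports:

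- *That false positives will certainly be far too frequent.* This needs a positive correlation, which is plausible but not shown.
- *That the plan commits to an uncorrected sandwich z-test, with still higher error rates.* Data analysis names generalised estimating equations and random effects. It does not name the variance estimator, small-sample correction or reference distribution, which an article commonly leaves to the analysis plan.
- *That opposing the two groups in a stratum is a further threat.* If groups in a stratum resemble each other, an unstratified standard error is too wide, if anything. Adding a 25% stratum share to a 25% village share brings the error down to about 6–7%. With group-level sharing the offset is small (10.5% to 9.8%).
- *That the 0.25 floor rules out a significant result.* It binds only a test based on the randomisation. The plan proposes model-based inference, which has no such floor but then relies on its independence assumption.

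Finally, Data analysis does not define its cluster. That it means the quartier is read from Study design and the Sample size calculation. If a separate analysis plan defines it as the allocated group, the analysis half of the point falls away. The misnamed unit and the power statement remain.

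**Conclusion.** The point holds in a conditional form. It follows from the article alone that six groups in three strata were allocated by three draws, that the quartier is misnamed as the randomisation unit, and that the power statement counts more independent allocated units than the design has. The equal-probability argument does not answer this.

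The consequence for inference has a direction but no known size. Positive correlation within villages or groups makes quartier-level standard errors too small. For shares of 25% to 50% the illustrative type I error is 7% to 17%, the low end assuming sharing within 10 villages and the high end sharing within the whole group. These figures rest on the assumed k, child-weeks, group sizes and village splits. The power loss is larger, because fewer degrees of freedom cost power even at zero correlation: at k = 0.20 and ρ = 0, power falls from 61% on 16 df to 44% on 4 df and 28% on 2 df.

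**What to change.** - In Study design, state that six village-based groups in three prevalence strata were allocated, and give the size and villages of each group.
- Include stratum in the primary model.
- Base the primary standard error on the allocated group, with a small-sample t reference on the reduced degrees of freedom (about 2 to 4). Give village-level clustering as a sensitivity analysis.
- Restate power as conditional on the within-group correlation, over a stated range.
- Note that a test based on the actual randomisation cannot give a two-sided p below 2/8 = 0.25, and present the result mainly as an estimate with its interval.

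The cost is wider intervals and a less favourable stated power. No new data are needed.
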